## Background

The association of chemotherapy (CT) and radiotherapy (RT) is the most frequent treatment approach for head and neck cancer (HNC) in cases of locally advanced disease [1]. Oral mucositis (OM) is the main side effect of RT and chemoradiation therapy (CRT) for HNC, its severity dependent on the number of RT sessions [2–6]. OM is an inflammatory reaction that can affect the entire oral cavity and gastrointestinal tract [7–10]. Intense pain, the need for nutritional supplementation, a higher number of clinical appointments and treatment interruption are common events associated with severe OM. These side effects may influence the survival rate and increase the costs of the HNC treatment [3, 5, 11–14].

CT and RT increase the levels of reactive oxygen species that may cause upregulation of transcription factors, such as NF-κB and STAT3 [4]. This increased level of transcription factors activates the production of inflammatory cytokines, such as matrix metalloproteinase, leading to tissue damage [4, 5, 15]. The use of photobiomodulation therapy (PBMT) has been encouraged and is described as effective therapy for OM treatment [16, 17]. Recent data showed that PBMT improves quality of life (QoL) and is effective in the control of OM, reducing the morbidity and costs associated with OM [16–24]. Oberoi et al. [18] concluded that PBMT reduced the number of severe OM episodes and pain associated with it. However, several protocols for PBMT have been described with differences in the laser wavelength, time of irradiation, frequency and energy used. They suggested that research should be conducted investigating the ideal parameters and clinical viability.

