### Participants

The participants will be HNC patients of the Brazilian public health system—Brazilian Unified Health System (Sistema Único de Saúde (SUS))—who will be treated with RT, with or without CT, in Araujo Jorge Hospital, Goiânia, Goiás, Brazil. To estimate the study sample size, we used the OpenEpi online calculator (http://www.openepi.com). The 95% significance level (1 – α error type I), a study power of 80% (1 – β error type II) and a 1.0 ratio of unexposed/exposed were set as estimator parameters. Finally, we considered a prevalence of severe OM of 60% for the control group and 21% for the PBMT group (OR = 0.18) [18]. The calculated minimum sample size was 50 participants (25 per group) and an additional 10% was considered to compensate for possible loss to follow-up.

Individuals older than 18 years of age of both sexes will be included in the study, edentulous or not, with neoplastic lesions in the head and neck site (oral cavity, oropharynx, nasopharynx and advanced stage laryngeal tumors; T3 N1 or T3 N2 and T4 with any N status). All participants will be subjected to RT (with or without CT), with a minimum dose of 50 Gy, 2 Gy/day and five times per week, in the conventional scheme of RT. All patients will be treated with the Elekta Compact (Elekta AB, Stockholm, Sweden), a linear accelerator that generates photon radiation with fixed energy of 6 MV. Participants will be excluded if they present with an infection or salivary gland tumors, Sjögren’s syndrome, are submitted to palliative treatment or were previously treated with RT and/or CT in the head and neck area. Individuals diagnosed with lymphoma, melanoma or skin cancer will also be excluded.

In this hospital setting, every HNC patient who will be submitted to RT must be evaluated by the Dental Care Service to obtain authorization before starting the HNC treatment. On this occasion, the individuals will be invited to participate in the study. After acceptance, the principle researcher will obtain a signed written informed consent form from the participants. Participants will be excluded from the trial in cases of death, withdrawal or absence from five or more laser therapy sessions.

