### Randomization and blinding/masking

Participants will be randomly assigned into two groups: group 1 (PBMT, five times per week) and group 2 (control). A computer-based random number generator (www.randomizer.org) will be used to assign the participants to the study groups. Simple randomization will be performed with an allocation ratio of 1:1. The sequence will be generated by an independent collaborator. The letters A and B will be used to determine the group: A = intervention and B = control. The sequence will be concealed in consecutively numbered opaque envelopes. Each envelope will be opened at the time of the first RT session. The participants will be blinded to the allocation group. In the control group, a sham laser will be used; the participants will hear the characteristic sound of the equipment but no irradiation will be performed. The researcher responsible for assessing the OM will also be blind regarding the study group and will not have contact with the participants since the assessment will be carried out using the photographs of the participants.

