#### Group 2: control group

The participants in the control group will have laser therapy appointments; however, they will not be irradiated. A simulation of the irradiation will be conducted by turning on the equipment, which produces the characteristic sound of the laser device, but the laser will not be irradiated. As mentioned for the PBMT group, if participants present with severe OM at the end of treatment, they will be submitted to PBMT. The participants will also be submitted to laser therapy in cases of RT suspension due to severe OM, during the suspension interval, to speed up the healing process.

The participants in the control group will be submitted to the dental care protocol. This protocol consists of elimination of the infection focus, a fluoride rinse, a chlorhexidine 0.12% rinse three times a day diluted in water in a 1:1 proportion, a recommendation to drink at least 1.5 L of water and the maintenance of good oral hygiene. In the presence of OM, Gingilone (Farmasa), an oral ointment with hydrocortisone 5 mg, neomycin 5 mg, troxerutin 20 mg, ascorbic acid 0.5 mg and benzocaine 2 mg, will be used. At the end of the RT treatment, the participants in this group will also receive PBMT if needed.

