In a recent study, Sonis et al. [54] discussed the effect of PBMT on tumor growth, proliferation, local invasion, metastases and the treatment response of the tumor. Based on the results of the studies that suggested upregulation and downregulation of genes and pathways associated with these aspects, and the lack of strong evidence regarding the safety of use of PBMT, the authors discouraged the use of PBMT as a treatment for OM. However, to date, the Multinational Association of Supportive Care in Cancer and the International Society of Oral Oncology still consider and recommend PBMT as an intervention for OM [55]. Use of PBMT is also associated with a lower frequency of interruption of the oncological therapy, and this may play an important role in the prognosis and chance of cure for the patient [24]. Corroborating these studies, Antunes et al. [56] showed that HNC patients who were submitted to PBMT presented a tendency of better overall and disease-free survival when compared with patients submitted to placebo. Additionally, the progression-free survival was significantly higher among patients submitted to PBMT and a better response to HNC treatment was observed. We believe it is important to study the effects of PBMT on inflammatory mediators and oxidative stress, so that a safety protocol and guideline can be established and proposed. Additionally, the diversity of PBMT protocols reported in the literature make it difficult to discuss the results from the different studies.

Finally, the effectiveness of PBMT is well established in the literature. This investigation aims to establish a safety evidence-based protocol for the use of PBMT in the treatment and prevention of severe OM, mainly in the public health system. The results of the investigation will be important to public policy-makers since they may enhance understanding regarding the costs involved in OM treatment and prevention with PBMT, favoring better resource allocation. Additionally, the investigation is also important to HNC patients since the results will encourage the incorporation of PBMT into the public health system, resulting in a better QoL for the patients during treatment.

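### Randomised participants who die, withdraw or miss five or more laser sessions are excluded from the trial, and these exclusions may be related to both severe OM and treatment arm

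*Protocol article*

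**What the plan says.** The rule stands in the Participants section of the protocol article: "Participants will be excluded from the trial in cases of death, withdrawal or absence from five or more laser therapy sessions". Under Randomization and blinding/masking, "Each envelope will be opened at the time of the first RT session", and the Group 1 section starts laser at that same session. Absence from laser sessions can therefore only build up after allocation. The rule can act in both arms because of the sham procedure: "The participants in the control group will have laser therapy appointments; however, they will not be irradiated".

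The article also links the relevant events to the outcome and to the arm:

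- Background, on severe OM: "Intense pain, the need for nutritional supplementation, a higher number of clinical appointments and treatment interruption are common events associated with severe OM". It continues: "These side effects may influence the survival rate and increase the costs of the HNC treatment".
- Discussion, on the arm: "Use of PBMT is also associated with a lower frequency of interruption of the oncological therapy".
- Group 2 section: controls receive laser "in cases of RT suspension due to severe OM", during the suspension interval. The Group 1 section states no corresponding provision.

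Under Costs due to severe OM, the cost items are severe episodes, hospitalisations, opioids and parenteral nutrition, taken from hospital records. Under Cost-effectiveness analysis, the ICERs divide the cost difference by the difference in severe-OM frequency, or by the difference in QoL change from baseline to the 30th RT session. No section names an as-randomised analysis set. The only allowance for losses is 10% extra recruitment.

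**The concern.** Removing participants after randomisation is harmless only if removal is unrelated to outcome and arm. The article's own statements point the other way. Interruption is described as common with severe OM and as less frequent with PBMT, and it is one plausible route to missed sessions. Five absences amount to one week of a five-per-week schedule, or 20% of the shortest eligible course (50 Gy at 2 Gy per day is 25 sessions; 5/25 = 0.20). A participant with a bad week could cross the threshold.

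The rule may also act unequally by arm. Controls whose RT is suspended for severe OM still have laser sessions to attend, whereas the article does not say what happens to PBMT participants in the same position, nor whether a session counts as missed while RT is suspended.

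All components of the ICERs are exposed. Severe cases may leave the effect measure, their costs may leave the cost measure, and participants excluded before the 30th session have no QoL change. Extra recruitment replaces numbers but does not undo selection.

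**Working it through.** **Inputs from the article (Participants).** Severe OM 60% in controls and 21% with PBMT; alpha 0.05 (taken as two-sided); power 80%; ratio 1:1; 25 per group plus 10%. The article gives no exclusion rates, so those below are assumptions.

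**The plan's own figure.** With mean rate (0.60 + 0.21)/2 = 0.405, the Kelsey formula gives (1.960 + 0.842)² × 2 × 0.405 × 0.595 / 0.39² = 24.87, so 25 per arm and 50 in total. The stated size reproduces and is not in dispute. With all 25 per arm kept, power is 82.3%.

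**Effect of exclusion.** Let p be the true severe-OM rate in an arm, and let e_s and e_n be the probabilities of exclusion with and without severe OM. Among those kept:

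- fraction kept: k = p(1 − e_s) + (1 − p)(1 − e_n)
- analysed rate: p(1 − e_s)/k

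*Same exclusion probabilities in both arms, e_n = 0.05:*

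- e_s = 0.20: control 0.480/(0.480 + 0.380) = 0.558; PBMT 0.168/(0.168 + 0.7505) = 0.183; difference 0.375. Lost: 14.0% of controls, 8.2% of PBMT, 11.1% overall.
- e_s = 0.40: control 0.360/(0.360 + 0.380) = 0.486; PBMT 0.126/(0.126 + 0.7505) = 0.144; difference 0.343. Lost: 26.0%, 12.4% and 19.2%.

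Starting from 25 randomised per arm, power falls to 75.4% and 66.5% in these two cases.

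*Severe cases excluded in one arm only, e_n = 0:*

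- PBMT arm: e_s = 0.20 gives 0.60 − 0.168/0.958 = 0.425; e_s = 0.40 gives 0.60 − 0.126/0.916 = 0.462.
- Control arm: e_s = 0.20 gives 0.480/0.880 − 0.21 = 0.335; e_s = 0.40 gives 0.360/0.760 − 0.21 = 0.264.

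*No true effect, 60% in both arms.* Excluding 20% of severe cases in one arm only makes that arm's rate 0.480/0.880 = 54.5% against 60.0%, a spurious difference of 5.5 percentage points in favour of whichever arm lost cases.

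**Consequence for the ICER per severe case avoided.** If the cost difference is held fixed for illustration, the ICER is multiplied by 0.39 divided by the analysed difference:

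| Exclusion pattern | Analysed difference | ICER multiplied by |
|---|---|---|
| Both arms, 20% severe, 5% non-severe | 0.375 | 1.04 |
| Both arms, 40% severe, 5% non-severe | 0.343 | 1.14 |
| PBMT arm only, 20% / 40% severe | 0.425 / 0.462 | 0.92 / 0.84 |
| Control arm only, 20% / 40% severe | 0.335 / 0.264 | 1.16 / 1.48 |

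In practice the cost difference would move too, if excluded participants' costs were dropped. The article gives no figures from which to size that.

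**The case against.** The strongest reply is that the mechanism is not established, and several tempting readings do go further than the article:

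- *Severe OM causes these exclusions.* The Background speaks of association and of a possible influence on survival. Death and withdrawal in head and neck cancer can have other causes.
- *RT suspension makes controls miss laser sessions.* The Group 2 clause says the reverse: laser is given in that interval, so suspended controls need not accumulate absences. In the PBMT arm laser precedes each RT session, so it is unclear whether any session is due during a suspension.
- *The costliest cases are dropped.* This is an inference from the cost items. Hospitalisation is listed as a cost, not as a cause of missed laser sessions, and no figures are given.
- *The damage cannot be corrected afterwards.* The article does not say that data collected before exclusion are discarded. Photographs at the 7th, 14th and 21st sessions may already show severe OM, and hospital-record costs do not depend on laser attendance.

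It is also fair to say that an unseen analysis plan could define an as-randomised set, that the exclusion probabilities above are assumed, and that with equal probabilities in both arms the shift is modest and towards no effect.

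These limits stand and are reflected in the verdict. They do not remove the point. The article states an explicit exclusion rule rather than leaving the matter open, and its plain sense is removal. Bias needs only that exclusion be related to outcome and arm, and the Background and Discussion make both plausible. The differing Group 1 and Group 2 texts weaken one route in one arm, but leave the rule open to acting unequally.

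**Conclusion.** The point holds in this form: an explicit post-randomisation exclusion, with nothing stated to keep those participants in the analysis as allocated, can bias the severe-OM rates, the QoL change and the cost difference. That the rule exists and acts after randomisation is certain. That exclusion is related to outcome and arm is plausible on the article's own statements but not demonstrated.

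Direction and size cannot be known in advance. Under the assumed rates, the planned difference of 0.39 moves modestly towards zero when both arms lose cases with the same probabilities. It moves either way, by up to 0.07 upwards (0.462 − 0.39) or 0.13 downwards (0.39 − 0.264), when severe cases are lost from one arm only. With 25 per arm, 20% of severe controls is three people (0.20 × 0.60 × 25), so a handful of exclusions is enough. The rule should be changed: the trial is meant to inform a public funding decision and the remedy is inexpensive.

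**What to change.** Replace the exclusion sentence with wording to this effect:

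> Missing laser sessions does not end follow-up or remove a participant from analysis. All randomised participants are analysed in the arm assigned. OM, QoL and cost data are kept up to death or withdrawal of consent, with costs taken from hospital records where consent allows. Missing values in living participants are handled by a mixed model or multiple imputation. Death is handled by a separate prespecified rule: costs are counted to death, and neither QoL nor costs are imputed after it. Absence from five or more laser sessions defines only a per-protocol sensitivity analysis.

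State how a missed session is counted while RT is suspended, and reconcile the Group 1 and Group 2 texts on laser during suspension so that the per-protocol set has the same meaning in both arms. This concerns counting and analysis only; it asks for no change to laser or RT management. Report exclusions and reasons by arm. Recruitment began in August 2017, so for participants already excluded, retrieve existing photographs, questionnaires and hospital records where consent allows.

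The cost is an amendment, some continued data collection from participants who miss sessions, and an estimated effect that may be somewhat smaller. The sample size need not change on this account.

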### Randomization and blinding/masking

Participants will be randomly assigned into two groups: group 1 (PBMT, five times per week) and group 2 (control). A computer-based random number generator (www.randomizer.org) will be used to assign the participants to the study groups. Simple randomization will be performed with an allocation ratio of 1:1. The sequence will be generated by an independent collaborator. The letters A and B will be used to determine the group: A = intervention and B = control. The sequence will be concealed in consecutively numbered opaque envelopes. Each envelope will be opened at the time of the first RT session. The participants will be blinded to the allocation group. In the control group, a sham laser will be used; the participants will hear the characteristic sound of the equipment but no irradiation will be performed. The researcher responsible for assessing the OM will also be blind regarding the study group and will not have contact with the participants since the assessment will be carried out using the photographs of the participants.

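### Chemotherapy is neither balanced by the simple randomisation nor adjusted for in the stated analysis, so a chance imbalance can shift the severe-mucositis difference and its ICER by a modest amount

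*Protocol article*

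**What the plan says.** - **Case mix** (Protocol article, Participants): "All participants will be subjected to RT (with or without CT), with a minimum dose of 50 Gy". Patients with and without chemotherapy therefore enter one trial population.
- **Allocation** (Randomization and blinding/masking): "Simple randomization will be performed with an allocation ratio of 1:1". No blocks, strata or minimisation are named.
- **Size** (Participants): "The calculated minimum sample size was 50 participants (25 per group) and an additional 10% was considered to compensate for possible loss to follow-up". The planning rates for severe mucositis are 60% in the control group and 21% with photobiomodulation, a difference of 39 points.
- **Analysis** (Statistical analysis of data): groups are compared on clinical and demographic characteristics by Pearson chi-square, and on mucositis severity and cytokines by Mann–Whitney. No stratified or adjusted comparison is stated, and nothing follows from the chi-square result.
- **Economic use** (Cost-effectiveness analysis): the between-group difference in severe-mucositis frequency is the denominator of one ICER. Two more use the change in each quality-of-life score from baseline to the 30th session.

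**The concern.** The protocol itself treats chemotherapy as a cause of mucositis. Its Background says that chemotherapy and radiotherapy both raise reactive oxygen species, discusses chemotherapy-induced mucositis as an entity, and describes a common initiation process. A patient on chemoradiation may therefore start with a different risk of severe mucositis from a patient on radiotherapy alone.

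Unstratified allocation of about 50 patients leaves the chemotherapy share in each arm to chance. An unadjusted comparison then attributes any resulting risk difference to the laser. The chi-square test may flag an imbalance but does not correct it, and in a trial of this size it can miss one that matters. What is at stake is the accuracy of the estimated difference in severe mucositis and of the ICER built on it. The cost difference is exposed too, because it includes hospitalisation, opioids and parenteral nutrition.

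**Working it through.** **1. The plan's own figure.** Inputs from Participants: 60% v 21%, two-sided 5% (sidedness assumed), 80% power, ratio 1.0. The Kelsey formula, with mean rate 0.405, gives

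n = (1.960 + 0.842)² × 2 × 0.405 × 0.595 / 0.39² = 24.87, so 25 per group.

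This reproduces the stated 50. Power at 25/25 is 82.3%. The sample size is not in question.

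**2. How often the chemotherapy share is unbalanced.** The protocol gives no share, so 30–80% is assumed. For share q and 25 per arm, the standard deviation of the between-arm difference is √[q(1 − q)(1/25 + 1/25)]. That is √(0.25 × 0.08) = 0.141 at q = 0.5 and √(0.16 × 0.08) = 0.113 at q = 0.8. Simulation of 200,000 trials of 50 patients, with arm sizes also left to chance, gives:

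| Chemotherapy share (assumed) | SD of difference | P(≥10 points) | P(≥20 points) |
|---|---|---|---|
| 50% | 14.3 points | 49% | 17% |
| 60% | 14.0 points | 48% | 15% |
| 70% (30% is the same by symmetry) | 13.1 points | 45% | 13% |
| 80% | 11.4 points | 38% | 8% |

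**3. What a 20-point imbalance does to the estimate.** Shift = imbalance × added risk from chemotherapy. The protocol gives no figure for the added risk, so 20, 30 and 40 points are assumed. The ICER column holds the cost difference fixed and takes 39 points as the true difference.

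| Added risk (assumed) | Shift | Share of the planned 39 | Observed difference | Change in ICER |
|---|---|---|---|---|
| 20 points | 0.20 × 20 = 4 | 10% | 35 or 43 | 39/35 = +11%; 39/43 = −9% |
| 30 points | 0.20 × 30 = 6 | 15% | 33 or 45 | 39/33 = +18%; 39/45 = −13% |
| 40 points | 0.20 × 40 = 8 | 21% | 31 or 47 | 39/31 = +26%; 39/47 = −17% |

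**4. Effect on false positives.** With no treatment effect and 25 per arm, a two-sided test of proportions rejects in about 7–8% of trials that have a 20-point imbalance (for example 15 v 10 chemoradiation patients). It rejects in about 4–6% of balanced trials. These rates are conditional on the imbalance; over all randomisations the error rate is preserved.

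**The case against.** The strongest reply is that simple randomisation is a legitimate choice. It is unbiased, chance imbalance is already covered by the overall type I error, and it keeps the next allocation unpredictable to a laser operator who knows the groups. The size of the effect also rests on two figures that the protocol does not supply. Covariate adjustment is often left to an analysis plan, which is not shown here. All of this stands, and it limits the point to an improvement of the stated analysis.

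Three stronger readings are tempting, and the document does not support them.

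- **Open-ended radiotherapy dose distorts the outcomes.** The Background says of mucositis that "its severity dependent on the number of RT sessions", and eligibility sets only a minimum dose. But mucositis and quality of life are assessed at fixed sessions, the last being the 30th, at 2 Gy per day for everyone. Patients assessed at a given session have had the same number of sessions. Dose beyond 30 × 2 = 60 Gy comes after the last scheduled assessment and cannot affect it. Patients planned for 25–29 sessions would not reach that assessment, but randomisation does not cure that.
- **Missing exactly 25 per group matters.** The calculation assumed that "a 1.0 ratio of unexposed/exposed were set as estimator parameters", and an exact 25/25 split has a probability of only 11% at N = 50. Yet a 20/30 split still has 80.3–81.2% power, and the average under simple randomisation is 81.5%, above the 80% target, before counting the 10% addition.
- **Imbalance could pass for the laser effect.** On the assumed ranges a 20-point imbalance moves the estimate by 4–8 points, and it favours photobiomodulation only half the time. It cannot by itself produce a 39-point difference.

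**Conclusion.** The point holds as a modest one. The design is valid, but the stated comparison ignores a factor that the protocol itself regards as a cause of mucositis. An imbalance of 20 points or more in chemotherapy share has a probability of about 8–17% (share of 30–80% assumed). At 20 points it shifts the severe-mucositis difference by about 4–8 points of the planned 39 (added risk of 20–40 points assumed). The ICER feels this more than the significance test does: the middle case moves it by −13% or +18% with cost held fixed, and the only sensitivity analysis stated concerns parameters of the laser therapy, not case mix. If chemotherapy adds little risk in this population, the shift shrinks in proportion.

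**What to change.** For all participants, whatever the stage of enrolment:

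- Compare severe mucositis with stratification by chemotherapy (yes/no), for example by a Mantel–Haenszel risk difference. Use a van Elteren test, the stratified form of the Mann–Whitney test, for mucositis grade. Planned chemotherapy, as known at allocation, is the safer stratifier because it cannot be affected by treatment.
- Compare quality of life with adjustment for chemotherapy and the baseline score.
- Use the adjusted differences in the ICERs, treating the cost difference in the same way.
- Describe baseline characteristics by group, and drop the chi-square test as a judge of balance.

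This needs no extra patients or visits, only a recorded treatment variable and a revised analysis paragraph. It should be fixed before outcomes are compared by group.

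Optional, and only if enough patients remain to be enrolled (recruitment began in August 2017): permuted blocks of varying, concealed size, stratified by planned chemotherapy and prepared by the same independent collaborator. In a simulation with blocks of 4 and N = 50, arm sizes differed by at most 2 and chemotherapy shares by at most about 6–7 points (shares of 50% and 70% assumed). The cost is a new set of envelopes and allocation that is more predictable to the unblinded laser operator.
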